## Abstract

**Background:**

The Researching Effective Approaches to Cleaning in Hospitals (REACH) study will generate evidence about the effectiveness and cost-effectiveness of a novel cleaning initiative that aims to improve the environmental cleanliness of hospitals. The initiative is an environmental cleaning bundle, with five interdependent, evidence-based components (training, technique, product, audit and communication) implemented with environmental services staff to enhance hospital cleaning practices.

**Methods/design:**

The REACH study will use a stepped-wedge randomised controlled design to test the study intervention, an environmental cleaning bundle, in 11 Australian hospitals. All trial hospitals will receive the intervention and act as their own control, with analysis undertaken of the change within each hospital based on data collected in the control and intervention periods. Each site will be randomised to one of the 11 intervention timings with staggered commencement dates in 2016 and an intervention period between 20 and 50 weeks. All sites complete the trial at the same time in 2017. The inclusion criteria allow for a purposive sample of both public and private hospitals that have higher-risk patient populations for healthcare-associated infections (HAIs). The primary outcome (objective one) is the monthly number of *Staphylococcus aureus* bacteraemias (SABs), *Clostridium difficile* infections (CDIs) and vancomycin resistant enterococci (VRE) infections, per 10,000 bed days. Secondary outcomes for objective one include the thoroughness of hospital cleaning assessed using fluorescent marker technology, the bio-burden of frequent touch surfaces post cleaning and changes in staff knowledge and attitudes about environmental cleaning. A cost-effectiveness analysis will determine the second key outcome (objective two): the incremental cost-effectiveness ratio from implementation of the cleaning bundle.

The study uses the integrated Promoting Action on Research Implementation in Health Services (iPARIHS) framework to support the tailored implementation of the environmental cleaning bundle in each hospital.

**Discussion:**

Evidence from the REACH trial will contribute to future policy and practice guidelines about hospital environmental cleaning. It will be used by healthcare leaders and clinicians to inform decision-making and implementation of best-practice infection prevention strategies to reduce HAIs in hospitals.

**Trial registration:**

Australia New Zealand Clinical Trial Registry ACTRN12615000325505

## Background

Healthcare-associated infections (HAIs) are a major cause of avoidable costs, morbidity and deaths among hospital patients [1]. In Australia, 200,000 cases of HAI arise each year and 1.9 million hospital bed days are diverted to treat them [1]. Reducing HAIs requires successful implementation of multiple evidence-based approaches [2].

While reasonable knowledge exists on many aspects of HAI prevention and control, good quality data on the effectiveness of hospital environmental cleaning programmes are limited. The healthcare environment plays a key role in the transmission of HAIs [3–5]. Environmental cleaning and evaluating cleanliness is therefore a critical component of HAI prevention. Most research examining the association between cleaning and reduction of infections has been based on a single ward or hospital using quasi-experimental designs [6]. There is little published evidence on cleaning relating to intervention cost, cost-effectiveness, feasibility and acceptability. Decision makers need more rigorous evidence from randomised controlled trials in real-world settings [7].

Environmental cleaning in hospitals is a complex process, and implementing and sustaining effective cleaning programmes is challenging [4, 8]. A review of hospital cleaning in Australian hospitals found great heterogeneity in cleaning practices between hospitals even though there are detailed cleaning guidelines [9, 10].

### Using bundles to improve implementation of complex interventions

A bundle is a set of evidence-based practices that when performed collectively and reliably have a proven ability to improve patient outcomes [11]. Using a bundle is a structured way to introduce a number of interventions concurrently, improving implementation and impact on processes of care.

An environmental cleaning initiative that combines multiple evidence-based interventions within a ‘cleaning bundle’ has the potential to improve the effectiveness of hospital cleaning by including strategies to educate, provide feedback and empower healthcare workers. A multi-site trial of an environmental cleaning bundle will allow a change in cleaning policy and practice to be evaluated in real-world settings to determine efficacy and cost-effectiveness. This trial will provide evidence that can be used by clinicians and decision makers to inform future environmental cleaning and infection prevention in hospitals. This trial is called Researching Effective Approaches to Cleaning in Hospitals (REACH).

### Trial objectives

#### Objective 1

The first objective is to evaluate the effectiveness of an environmental cleaning bundle to reduce HAIs in Australian hospitals.

#### Objective 2

The second objective is to estimate the cost-effectiveness of a decision to adopt the environmental cleaning bundle for Australian hospitals.

## Methods/design

### Study design

#### Stepped-wedge design

This is a randomised controlled trial using a cross-sectional stepped-wedge random allocation [12]. There will be sequential roll-out of an environmental cleaning bundle intervention to 11 Australian public and private hospitals over 62 weeks. Example trial timings are shown in Fig. 1.

**Fig. 1 Fig1:**
[figure not shown]
Example stepped-wedge trial timings over 62 weeks in 11 Australian hospitals

All hospitals will receive the intervention and act as their own control, with analysis undertaken of the change within each hospital based on data collected in the control and intervention phases. The stepped-wedge design, with staggered commencement timings and intervention length (20–50 weeks), supports feasibility while maintaining the rigour of the study. This design will allow research staff to work with individual hospitals as they change-over, maximising consistency of implementation of the cleaning bundle and avoiding managing change at 11 sites across Australia simultaneously. This design also avoids having control hospitals that get no intervention, which could make it difficult to recruit hospitals, and ensures equity. Each hospital acting as their own control avoids inconsistencies in comparing infection control programmes across hospitals and jurisdictions.

#### Implementation framework

The project will use the integrated Promoting Action on Research Implementation in Health Services (iPARIHS) [13] framework to promote the successful implementation of the evidence-based intervention at trial sites [14]. This framework has key constructs of innovation (e.g. the cleaning bundle), recipients (e.g. the environmental services staff) and context (e.g. hospital characteristics) that are underpinned by a fourth construct of facilitation (e.g. engagement strategies) [13].

### Study population

Eleven large acute public and private Australian hospitals that fulfil the inclusion criteria and agree to participate will be enrolled in the study. These criteria are that each hospital:Has an intensive care unit (ICU) accredited for advanced clinician training by the College of Intensive Care Medicine of Australia & New Zealand [15]Is classified by the National Health Performance Authority (NHPA) as a major hospital (public hospital) or has over 200 in-patient beds (private hospital) [16]Has an established HAI surveillance programme that collects data on *Staphylococcus aureus* bacteraemia (SAB) infections, *Clostridium difficile* infections (CDIs) and vancomycin resistant enterococci (VRE) infections

#### Recruitment

The study team will list all eligible sites then order the list to ensure (i) a representation of both private and public hospitals and (ii) representation from at least four Australian states and territories. The recruitment process will purposively select and approach eligible hospitals to optimise the feasibility and practicality of completing the trial.

### The intervention

#### Developing and piloting

In 2014, [name] and colleagues, from the National Health and Medical Research Council (NHMRC) Centre of Research Excellence in Reducing Healthcare Associated Infections (CRE-RHAI), conducted a single-site pilot of an environmental cleaning behavioural change bundle. The bundle components were agreed, following a review of the evidence and feasibility, by an expert panel and piloted successfully at a large acute hospital in Queensland in 2014 [17]. The pilot study demonstrated that the intervention is acceptable to hospital staff, that the outcomes can be reliably measured and that the cleaning bundle is feasible [17].

#### Implementation

The study team will use the iPARIHS framework to support effective implementation of the cleaning bundle intervention at each site [13, 14]. A tailored intervention should optimise bundle implementation and compliance. The tailoring will not compromise the integrity of the individual components and the ‘sum of the whole’ of the bundle.

Initially, we will map the hospital characteristics and context (e.g. staffing, size), infection prevention policies and practices (e.g. antimicrobial stewardship, antibiotic use, screening) and conduct surveys. This will provide the information to develop a tailored implementation strategy for each site, based on behavioural change and adult learning principles, current environmental cleaning practices and other contextual factors.

Throughout the trial, we will monitor these characteristics and other relevant activities (e.g. cleaning staff changes, policy changes) within the hospital. Ongoing reviews of contextual information throughout the intervention at each site will assist with trial site comparisons, replication and scalability and knowledge translation.

### Randomisation

Hospitals will be randomly allocated to intervention timing once 11 sites have been enrolled. One of the chief investigators ([name], statistician) will be responsible for computer generation of the allocation times and the allocation of hospital identifiers. Hospitals will be informed of their intervention start date 12 weeks before the intervention commences. This 12-week period will include 4 weeks of establishment/engagement activities (‘establishment phase’) and 8 weeks of baseline data collection (‘control phase’). Hospitals and research sites will not be blinded because it is not possible to blind the cleaning staff to the intervention.

### Outcomes and data collection: objective 1: effectiveness of the environmental cleaning bundle

Objective 1 outcomes and measures are shown in Table 2.

**Table 2 Tab2:** Objective 1 outcomes and measures

Outcome	Measure	Method
Primary outcome		
Healthcare-associated infection (HAI) rates in each trial site	Numbers of *Staphylococcus aureus* bacteraemia (SAB), *Clostridium difficile* infection (CDI) and clinical isolates of vancomycin resistant enterococci (VRE) and monthly rates per 10,000 occupied bed days	Datasets include all patients across the hospital with a HAI, and data on occupied bed days Collated from: - Hospital infection data and reports for ongoing surveillance - Hospital occupied bed days reports
Secondary outcome		
Hospital cleaning performance—thoroughness of hospital cleaning in each trial site	Number and percentage of ultraviolet (UV) gel dots removed completely following cleaning	DAZO® Fluorescent Marking Gel dots applied to frequent touch sites around two patient cubicle and bathroom areas in the intensive care unit (ICU) and the highest risk wards
Other outcomes—study specific data set		
Bio-burden of frequent touch surfaces post cleaning	Levels of organic matter in relative light units (RLUs) post cleaning in three hospitals	Adenosine tri-phosphate (ATP) bioluminescence measurements
Other outcomes—study specific data set		
Changes in staff knowledge and attitudes around environmental cleaning	Pre-intervention educational needs. Pre- and post-intervention knowledge and attitudes about environmental cleaning and job roles	Environmental services staff questionnaires and discussion groups
Other outcomes—existing data set		
Changes in rates of screening and clinical isolates	Numbers of positive clinical isolates of other multi-resistant organisms per 1000 patient days at risk	Collated from hospital infection data and reports, where available for ongoing surveillance and supplied to project team by trial site team
Other outcomes—existing data set		
Changes in patients’ perception of hospital cleanliness	Patients’ perceptions of cleanliness	Collated from existing hospital-based survey data, where available and supplied to project team by trial site team

#### Primary outcome—HAI rates

Whole hospital infection rates will be used as the primary outcome. This reflects the frequent movement of staff, patients and cleaners across hospitals wards and locations.

Hospitals will collect monthly data and then submit it at least bi-monthly to the project team. The numbers of SABs, CDIs and clinical isolates of VRE will be monitored, and rates calculated using algorithms based on nationally agreed definitions, as published by the Australian Commission on Safety and Quality in Health Care (ACSQHC) [25].

#### Secondary outcome—thoroughness of routine hospital cleaning

Thoroughness of hospital cleaning will be measured using the DAZO® Fluorescent marking gel and ultraviolet (UV) light system that dries on surfaces following application and resists dry abrasion but is removed with standard cleaning. A trial site staff member trained by the study team will apply the gel dots on frequently touched points in the patient cubicles as per the Centers for Disease Prevention and Control Environmental Cleaning Checklist [26]. On each audit occasion, dots will be placed in two different beds and bathroom areas in the ICU and in at least 50 % of the hospital trial site wards. Wards will be prioritised according to NHPA risk factors for patient vulnerability [16]. Cleaning staff will be aware of the frequently touched points but will not be aware of where the dots are actually applied or the timing of audits.

After cleaning, the dot locations will be checked using the UV light pen, which will show the extent of removal of the dot by cleaning. All results will be entered directly into a web-based application on a mobile device at the time of data collection. Cleaning audits will take place in the control and intervention periods. Feedback mechanisms for staff will be implemented as part of the bundle during the intervention period.

#### Other outcomes

##### Bio-burden of frequent touch surfaces

We will routinely assess bio-burden on a selection of high touch surfaces using adenosine tri-phosphate (ATP) luminosity following cleaning in three of the 11 hospitals, using a validated sampling process [27].

##### Knowledge and attitudes of environmental cleaning staff

The knowledge and attitudes of environmental cleaning staff will be surveyed pre- and post-intervention and will serve two purposes. First, it will provide an understanding of baseline hospital context, including knowledge, attitudes and practices of environmental services staff, which will be used to tailor the educational component of the cleaning bundle. Second, it will allow a comparison of knowledge and attitudes about environmental cleaning between the pre- and post-intervention phases. This is particularly important to gauge whether the bundle has impacted not only upon behaviour but also on attitudes and knowledge, which are the longer-term drivers of behavioural outcomes.

##### Other surveillance data

In areas of the hospital where patient screening for multi-resistant organisms is a standard practice (such as in ICU) and consistently undertaken during the study period, data on screening isolates, via nasal swabs for Methicillin-resistant *Staphylococcus aureus* (MRSA) and stool or peri-rectal swabs for VRE per 1000 patient days, will also be collated.

##### Patient satisfaction surveys

These will only be used if an existing survey tool and process is used by the hospital and if patient survey collation/report periods align with the control and intervention timings at that trial site.

#### Power calculation

Eleven hospitals with a pre-intervention infection rate (a combination of SAB, CDI and VRE infections) of 5 per 10,000 patient days will give us 86 % power to detect a 20 % post-intervention reduction in infection risk. This is based on a two-sided 5 % significance level, a within-hospital correlation in infection rates of 0.3 and the intervention timings shown in Fig. 1. The pre-intervention infection rate and within-hospital correlation were estimated using a dataset of over two million hospital admissions and infection data from nine Queensland hospitals [28]. The stepped-wedge sample size formula is from Hussey and Hughes [29]. We assumed no delay in the treatment effect for the sample size calculation, that is, rates decline as soon as the intervention begins.

To detect an increase in the secondary outcome (thoroughness of cleaning) from 82 to 87 % due to the intervention with a 92 % power requires only five hospitals with 40 observations per hospital per 4 weeks. This is based on the pilot data and recent studies [17, 22, 30, 31]. This secondary hypothesis requires far fewer hospitals because the outcome of cleaning failure is likely to be more common than HAIs (primary outcome), which are relatively rare.

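### The 92% power claimed for cleaning thoroughness with five hospitals does not fit the 8-week control phase; on that schedule it is about 65–77%, and 92% needs about 9 to 10 hospitals

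*Protocol article*

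**What the plan says.** The second paragraph of the Power calculation section gives the target for thoroughness as an increase "from 82 to 87 % due to the intervention with a 92 % power" and says that this "requires only five hospitals with 40 observations per hospital per 4 weeks". It adds that this hypothesis needs many fewer hospitals than the primary one, because cleaning failure is more common than infection. It does not state the number of control blocks, the correlation or the treatment of time.

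Two other places fix the amount of control data. The Randomisation section divides the 12 weeks before changeover into 4 weeks of establishment and "8 weeks of baseline data collection", and labels the latter the control phase. The section on thoroughness of routine cleaning says: "Cleaning audits will take place in the control and intervention periods".

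The abstract gives "an intervention period between 20 and 50 weeks", and the Stepped-wedge design section describes roll-out "to 11 Australian public and private hospitals over 62 weeks". The Analysis section for thoroughness plans a binomial mixed model with intervention, dot location and a hospital random intercept. It lists no calendar-time term.

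**The concern.** Infection counts come from surveillance that already runs at each site. The gel-dot audits do not: trained site staff have to place and read the dots, and the protocol puts this work in the control and intervention periods. If the control period is the 8 weeks named under Randomisation, the control side of the comparison is small, and five hospitals at 40 observations per 4 weeks may not support 92% power.

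The sentence suggests a large margin: 11 hospitals enrolled where five would do. A team that relied on it could regard the loss of sites, which the Limitations section discusses as a risk, or lighter auditing as harmless for this outcome.

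**Working it through.** **Inputs from the protocol.** Proportions 0.82 and 0.87; 40 observations per hospital per 4 weeks, i.e. 10 per week; 8 control weeks; 20 to 50 intervention weeks (midpoint 35); 62 weeks in total; 11 hospitals.

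**Assumptions.** Starts fall every 3 weeks from week 12 (62 − 50) to week 42 (62 − 20), because Fig. 1 is not shown. Observations within a hospital are independent given its intercept. The test is two-sided at 5%; the protocol states this level ("This is based on a two-sided 5 % significance level") in the primary-outcome paragraph only. No correlation is given for thoroughness, so it was varied from 0 to 0.3.

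**Formula.** For n0 control and n1 intervention observations, unpooled:

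power = Φ( 0.05 / √(0.82×0.18/n0 + 0.87×0.13/n1) − 1.96 )

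**Step 1: reproducing the 92%.** Take the first five start dates (weeks 12, 15, 18, 21, 24) and suppose audits run in every week before changeover.
- Control weeks: 12+15+18+21+24 = 90, so n0 = 900.
- Intervention weeks: 50+47+44+41+38 = 220, so n1 = 2,200.
- Standard error: √(0.1476/900 + 0.1131/2,200) = 0.01468.
- 0.05/0.01468 − 1.96 = 1.45, so power is 92.6%.

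Five dates spread across the range give about 95–97% on the same basis. The printed figure can therefore be recovered, but only with audits in all pre-changeover weeks and no time effect.

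**Step 2: the 8-week control phase.** Five hospitals give n0 = 5×80 = 400 and n1 = 5×350 = 1,750.
- Standard error: √(0.1476/400 + 0.1131/1,750) = 0.02082.
- 0.05/0.02082 − 1.96 = 0.44, so power is 67%.

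Other variants with 400 control observations and no time term:

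| Method | Power |
|---|---|
| Pooled two-proportion test | 72% |
| Wald test on the logit scale | 74% |
| Random-intercept GLS, correlation 0 to 0.3, first, last or spread dates | 65–68% |
| Simulated logistic model with hospital terms | 72–75% |
| Logit scale, all five hospitals at the full 50 intervention weeks (n1 = 2,500) | 77% |

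The overall range is about 65–77%. None of these reaches 92%.

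**Step 3: can longer follow-up rescue it?** With unlimited intervention data only the control term remains: 0.05/√(0.1476/400) − 1.96 = 0.64, a ceiling of 74% (84% on the logit scale). The control phase is the limit, so the assumed spacing of start dates does not drive the result.

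**Step 4: hospitals needed.** With 80 control and 350 intervention observations per hospital and no time term:

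| Hospitals | Unpooled | Pooled |
|---|---|---|
| 5 | 67% | 72% |
| 8 | 86% | 89% |
| 9 | 90% | 92% |
| 10 | 92% | 94% |
| 11 | 94.5% | 96% |

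GLS gives 94% for 11 hospitals, simulation 96% and the logit-scale test 97%.

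**Step 5: sensitivity figure only.** If a calendar-time term were added, 11 hospitals with 8 control weeks would have about 79–86% power with linear time and 74–82% with 4-week period effects.

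**The case against.** **The sum is reproducible.** Step 1 recovers 92–93%, so this may be an unstated input and not a slip in arithmetic, and an article need not list every input. That stands as a description of the likely cause. It does not rescue the sentence, because the input that is needed conflicts with the control phase set out under Randomisation.

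**The true audit volume may exceed 40.** Dots go in two bed and bathroom areas in the ICU and in at least half of the wards, in large hospitals. At twice the rate (800 control and 3,500 intervention observations), five hospitals would reach 92.4% if all observations were independent. Dots within a room are unlikely to be independent, which would pull this down. In any case the printed claim is made at 40.

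**Enrolment is 11, and the primary outcome drives it.** Randomisation waits for 11 sites, and nothing in the protocol proposes using five or thinning the audits. This stands. It limits the consequence to a misleading justification.

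**A stronger reading to resist.** A reader might infer that even 11 hospitals fall short of 92%, because the power section says "The stepped-wedge sample size formula is from Hussey and Hughes [29", a design in which time is normally adjusted for. The protocol does not support this. The formula is named in the primary-outcome paragraph, and the thoroughness paragraph names none. The linear calendar term belongs to the infection-rate model, and the thoroughness model lists no such term. Whether it should have one is a separate question about the analysis, not an error in the stated power.

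**Conclusion.** The concern holds for the five-hospital claim. At 40 observations per hospital per 4 weeks, with 8 control weeks and the planned model, five hospitals give about 65–77% two-sided power, against the stated 92%. Reaching 92% takes about 9 to 10 hospitals, which is close to the number enrolled.

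The protocol does not show the trial to be underpowered for thoroughness: 11 hospitals give about 94–96% under the planned model. The time-adjusted 74–86% is conditional on a term that is not planned.

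These figures rest on start dates 3 weeks apart, independent observations within hospital and a two-sided 5% level. Clustering of dots within rooms would lower all of them; a higher audit rate would raise them.

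**What to change.** In the Power calculation section, delete the five-hospital statement and the sentence that this hypothesis needs many fewer hospitals. Replace them with the power for the 11 enrolled hospitals under the planned audit schedule (about 94–96% at the stated rate with 8 control weeks and no time term). State the number of control blocks, the observations per block, the correlation and the significance level used. If audits are in fact meant to run in all pre-changeover weeks, say so and reconcile this with the control phase under Randomisation. Optionally, report the power with a calendar-time term (about 74–86%) as a sensitivity figure, labelled as conditional.

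The cost is a few sentences and the loss of a favourable claim. No hospitals, audits or analyses need to be added.
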